## Abstract

Diabetes is a major public health problem, increasingly affecting low- and middle-income countries. The project CEAD (Contextualizing Evidence for Action in Diabetes in low-resource settings) aims to evaluate the implementation of comprehensive diabetes care in two low-resource settings in Ecuador and to stimulate context-led health systems innovations to improve diabetes care and reduce inequity. The mixed-methods approach includes a 24-month retrospective study to assess the current level of implementation of comprehensive diabetes care and participants will be followed up prospectively for two years to assess changes in healthcare and clinical outcomes from the outset of the research. We will include individuals diagnosed with type-2 diabetes aged over 18 years, who are accessing diabetes care in health facilities in the study districts. Varied stakeholders (patients and family members, community members, healthcare workers and decision-makers) will interpret the underlying causes of the observed weaknesses and propose solutions to strengthen diabetes-related healthcare in focus group discussions (FG). A second set of FG will analyze perceived improvements in healthcare based on prospective cohort findings and consider the success/failure of any context-led innovations occurring throughout the research. Our study will demonstrate how evidence can be contextualized to stimulate local innovations and overcome weaknesses of diabetes-related healthcare in low resource settings.

## 1. Introduction

Noncommunicable diseases (NCDs), such as diabetes, are a major global public health problem and are closely linked to poverty [1]. On one hand, NCDs are more prevalent among low-income population groups with NCDs, and on the other hand, people with NCDs have additional challenges in productivity which can impact economic development. Diabetes can lead to major health complications, as well as increasing the risk of all-cause mortality, especially among younger people of working age [2]. The growing burden of NCDs in low- and middle-income countries (LMICs) is threatening the capacity of health systems to respond adequately to the population’s needs [3]. Not only do LMICs bear 86% of the burden of NCD-related premature deaths [4], but they are home to 75% of people living with diabetes [5].

Diabetes treatment includes blood glucose control through a combination of diet and physical activity and, if necessary, medication. In addition, it is necessary to control blood pressure and lipids to reduce cardiovascular risk and carry out regular screening for retinopathy, nephropathy and diabetic foot to facilitate early treatment of diabetes complications [2]. Given that most evidence on how to manage and prevent NCDs is largely generated in high-income settings [6], it is possible that elements of successful control, such as the availability of a multidisciplinary team trained in diabetes management, or periodic assessment by medical specialists, may be difficult to apply in low-resource settings.

In this regard, a recently published study [7] found a total unmet need for diabetes care of 77% in low- and middle-income countries. Deficits were identified at diagnosis with a lack of testing, and during monitoring with sub-optimal levels of glycemic control. Most countries have national diabetes policies, but their level of implementation is variable. Less than half of countries with national guidelines for diabetes management report their full implementation [8]. For example, several studies show shortcomings in the implementation of key processes of diabetes care and glycemic control in LMICs [9,10]. Therefore, there is a need to develop clinical guidelines for chronic diseases that can be realistically applied in resource-constrained primary care settings [9]. In Ecuador, where diabetes was the second cause of death in 2018 [11], the Ministry of Public Health published its first Clinical Practice Guideline (CPG) for Type 2 Diabetes in 2017 [12]. This guideline includes recommendations for multidisciplinary disease management at primary, secondary and tertiary levels. It is an adaptation of the United Kingdom’s National Institute of Clinical Excellence (NICE) guidance [13]. However, it is not clear to what extent the measures in this guide are implemented in Ecuador or if there are resources at the local level to implement them.

Moreover, health systems require evidence to guide the best health policies and programs, as well as mechanisms to collaborate with communities. This collaboration allows a more effective response to health needs and facilitates communities in mobilization of resources and active participation in promoting and managing their health [3]. Authors have pointed out that health interventions also require implementation assessments to understand all the processes involved in the adoption and implementation of public health interventions and contextual factors which determine the outcomes of global health interventions [14].

This protocol, together with a previously published one [15], is part of a 5 year (2019–2023) European Research Council (ERC)-funded research project, “Contextualizing Evidence for Action in Diabetes in low-resource settings” (CEAD). It is an implementation science project whose overall objective is to explore the process by which global recommendations can be translated into context-specific, evidence-informed action for diabetes prevention in low-resource settings.

## 2. Materials and Methods

### 2.1. Research Goals

This study aims to evaluate the implementation of comprehensive diabetes care in two low-resource settings with different cultural, territorial, economic, and social conditions in Ecuador and to stimulate context-led health systems innovations to improve diabetes care and reduce inequity.

Specific aims:To evaluate the implementation of diabetes care according to the 2017 Clinical Practice Guideline [12] in two health districts in Ecuador.To use local knowledge and opinions to understand the observed weaknesses, their impact on health equity and identify how local health systems might be strengthened.To assess the feasibility and effectiveness (in the short-medium term) of context-led health systems innovations to improve diabetes care locally.

### 2.2. Setting

We will carry out the fieldwork for both quantitative and qualitative research in two low-resource settings in Ecuador with different territorial, cultural, social, and economic characteristics. We selected 2 health districts in the country: (1) District 17D06, Quito, an urban health district with 507,499 residents (est. 2017); and (2) District 08D02, in Esmeraldas Province, a rural area in the northern coastal region of the country with a population of 44,498 (est. 2017). The choice was based on several characteristics. Firstly, the capital and coastal areas of Ecuador have a high diabetes prevalence according to national statistics [16]. Secondly, the two regions chosen have vastly different socio-economic, environmental, and cultural profiles. Lastly, to improve the feasibility of the research, we focused the research in areas where we had contact with local researchers who were motivated to implement evidence-based diabetes care in the population.

### 2.3. Study Design

This is a mixed-methods study (registered 16 September 2019, NCT04560062). Firstly, we will carry out a retrospective cohort study to assess the current level of implementation of comprehensive diabetes care over a 2 year period (from January 2019 to December 2020), by describing the healthcare received (process) and the health outcomes of a representative sample of diabetes patients currently accessing healthcare in the study regions. Secondly, we will interpret underlying causes of the observed weaknesses through focus groups prompted by the findings of the cohort study. Finally, the findings from the retrospective cohort study and qualitative research will generate local innovations which will be evaluated through a prospective follow-up of the same cohort with the participants included in retrospective cohort. The innovations in the health system will not be funded by the research and operational aspects will not be supported by the study team (Figure 1).

Research assistants will obtain data mainly from health services records, which will be supplemented by patient interviews. Community health workers working with the CECOMET and MSP will be tasked to collect data in the District 08D02, in Esmeraldas Province. In District 17D06 in Quito, data will be collected by trained interviewers that will contact the patients identified at the health service sample. Firstly, after obtaining informed consent they will carry out the patient interview. It will include information on the patients’ socioeconomic and demographic situation (self-reported), their access to health services as well as some clinical aspects (both obtained from health service records) (Table 1). In addition, we will carry out two brief questionnaires: one regarding perceived social support (the Multidimensional Scale of Perceived Social Support [17,18] MSPSS) and another on health-related quality of life (the Diabetes Health Profile-18 [19]; DHP-18). We will also add to the interview questions about the healthcare provided to the patient (e.g., frequency of disease monitoring, glucose tests, and other medical examinations). We will perform a cultural and linguistical adaptation of the DHP-18 questionnaire and validate it prior to use.

Afterwards, we will collect data from electronic health service records. We will collect data regarding whether the patient attended health visits and underwent screening for diabetes complications as recommended in the 2017 CPG in Ecuador [12] and record the date and details of any complications experienced throughout the evaluation and other clinical data such as comorbidities, treatments, or patient management by a multidisciplinary healthcare team.

Patient files, laboratory, and pharmacy records will provide information on diabetes care, treatment, glycemic control and presence of comorbidities and diabetes complications. Data pertaining to the 2-year period from 1 January 2019 to 31 December 2020 will be extracted.Outcomes

The components of comprehensive diabetes care to be assessed were selected from the 2017 CPG in Ecuador [12]. The section on pre-diabetes is not included. We will not assess the appropriateness of pharmacological treatments. The health professionals included in the assessment will be multidisciplinary at the second and third level of care.

Primary outcomes (Table 2) are a collection of basic indicators and are divided into two sections:Disease control: Defined in two dimensions. Firstly, biochemical control based on the last laboratory result of glycated hemoglobin or blood glucose, recorded in the year of study. The second dimension will be health-related quality of life, assessed using the DHP-18 questionnaire previously validated in Ecuador.Access to healthcare: Care process indicators that represent the proportion of the patients who undergo the care processes recommended by the CPG to manage the disease. We will obtain the care frequency for each patient as a quantitative value and will also categorize those care indicators that are recommended with greater periodicity in the CPG.

Secondary outcomes include:3.Control of complication risk factors: Care result indicators that determine proportion of patients who meet the standards of diabetes care and the clinical objectives during the year of study (January 2019 to December 2020).4.Measurements of diabetes-related behaviors/conditions: Access to medication (self-reported) and social support obtained from a standardized questionnaire, and patient information received, self-reported.5.Resources used due to decompensation of the disease and/or complications.6.Disease complications (as indicators that measure the proportion of patients with complications occurring that could result from insufficient control of the disease).

More detailed information on outcomes is available on the ClinicalTrials (NCT04560062).Analysis

In the quantitative analysis of comprehensive diabetes care, we will include descriptive statistics according to variable type and will calculate the proportion of patients that received care as per the CPG recommendations and/or the proportion receiving an intermediate level of care (as required). Proportions will be described with 95% confidence intervals. Variation in healthcare received and diabetes-related health will be described using sociodemographic and clinical characteristics of the patients to highlight potential inequities. A multivariate logistic regression model may be used to explore the relationship between the primary outcomes and socioeconomic explanatory variable and/or type of health facility. If necessary, we will adjust for potential confounders such as patient factors (e.g., sex, age, comorbidity, perceived social support) and/or environmental factors (e.g., proximity to the health center, availability of different medical specialties or methods as laboratory test).

Steps will be taken to prevent missing data (e.g., we will access data from different sources such as records of primary, specialized and hospital care), but some level is unavoidable and we will incorporate methods analyzing missing data or data from uncertain sources when necessary [20,21].

Statistical analysis will be performed using Stata Version 15 (StataCorp LP; College Station, TX, USA).

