#### 2.3.4. Cohort Follow-Up

Study population:

The patients selected for the retrospective cohort study (described above) will form the prospective cohort population.Data collection procedure:

Data collection tools will be identical to those used for the retrospective cohort study. Clinical files will be reviewed every 12 months for the duration of follow-up (2 years) (Table 1).Outcomes:

Outcomes will be the same as for the retrospective cohort study (Table 2). We will assess changes in the indicators selected during the follow-up study.Analysis:

Any innovation in packets of care offered and how to organize healthcare services will be recorded and described in detail. Analysis will center on changes in the core indicators over time. Because this is not a controlled randomized intervention, we will not attempt to test whether changes are statistically significant.

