**Figure 2 ijerph-18-03391-f002:**
[figure not shown]
Purposive selection criteria for focus group participants and axes for discussion of diabetes care implementation challenges.

**Table 1 ijerph-18-03391-t001:** Summary of routinely collected data.

Type of Data		Time Point			
Category	Specific Information	Baseline	Retrospective (2 years)	Prospective	
				Year 1	Year 2
Demographic data	Date and country of birth	X			
	Sex	X			
	Ethnicity	X			
	Marital status	X			X
Socioeconomic data	Education	X			X
	Employment status	X			X
	Household income	X			X
Data on access to health services	Primary care consultations		X	X	X
	Specialist consultations ^1^		X	X	X
	Number of biochemical analysis ^2^		X	X	X
	Number of blood pressure records		X	X	X
	Number of BMI records		X	X	X
Clinical data	Date of diabetes diagnosis	X			
	Diabetes-related hospitalizations		X	X	X
	Diabetes-related medical assistance		X	X	X
	Biochemical results ^2^		X	X	X
	Results of physical measurement		X	X	X
	Medications ^3^		X	X	X
	Diabetes complications ^4^		X	X	X
Access to treatment (self-reported) ^5^		X			X
Perceived social support (MSPSS) ^5^		X			X
Health-related quality of life (DHP-18) ^5^		X			X

^1^ Nutritionist, psychologist, and/or physiotherapy. ^2^ Glucose, glycated hemoglobin, lipid profile (cholesterol, triglycerides, HDL, LDL), renal function (creatinine, glomerular filtrate, albuminuria). ^3^ Treatment of diabetes or other chronic pathologies. ^4^ Retinopathy and/or blindness, lower limb amputations, cardiovascular events, and renal dysfunction. ^5^ Reassessment in the final 6 months of follow-up. Abbreviations: BMI: body mass index MSPSS: The Multidimensional Scale of Perceived Social Support, DHP-18: The Diabetes Health Profile-18.

**Table 2 ijerph-18-03391-t002:** Study outcome measures.

Primary Outcomes		Secondary Outcomes	
Outcome	Definition	Outcome	Definition
**A. Disease control**		**C. Control of complication risk factors over the 12-month period**	
1. Biochemist	Proportions of patients with biochemically controlled diabetes ^3^	1. Blood pressure control	Proportion of patients with blood pressure < 140/90 [12]
2. Health-related quality of life	Individual score of the Diabetes Health Profile-18 [19].	2. Weight control	Proportion of patients with BMI between 18.5 kg/m^2^ and 25 kg/m^2^ or 5% weight loss [12]

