^1^ We will provide both the continuous and categorized value for data analysis. ^2^ Evaluation period: time since diabetes diagnosis. ^3^ Controlled diabetes: HbA1C < 7% or HbA1C < 8% if ≥15 years of evolution or complications and serious comorbidities; or fasting blood glucose: 70–130 mg/dL or postprandial blood glucose < 180 mg/dL [12,24]. Pregnant women: fasting blood glucose: 60–99 mg/dL or postprandial blood glucose: ≤140 mg/dL (1 h after eating) or ≤120 (2 h after eating) [25]. ^4^ MDRD-4 formula not validated for pregnant women [26]. Abbreviations: GP: general practitioner; CPG: Clinical Practice Guideline; HbA1C: glycated hemoglobin; BMI: body mass index; HDL: high-density lipoprotein; LDL: low-density lipoprotein.

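### Biochemical control (A1) is followed up only as a controlled/not-controlled proportion, although HbA1c values are collected in every period: gains that do not cross the target go unrecorded, and status can change without a fall in HbA1c

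*Protocol article*

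**What the plan says.** Section 2.3.1 (Outcomes) sets out "biochemical control based on the last laboratory result of glycated hemoglobin or blood glucose, recorded in the year of study". Table 2, outcome A1, gives its form: "Proportions of patients with biochemically controlled diabetes". Footnote 3 of Table 2 supplies the cut-offs: "Controlled diabetes: HbA1C < 7% or HbA1C < 8% if ≥15 years of evolution or complications and serious comorbidities". It adds alternative ranges for fasting and postprandial glucose and separate limits in pregnancy.

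Table 1 marks biochemical results for the retrospective period, Year 1 and Year 2. Its footnote 2 lists what these are: "Glucose, glycated hemoglobin, lipid profile (cholesterol, triglycerides, HDL, LDL), renal function (creatinine, glomerular filtrate, albuminuria".

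Footnote 1 of Table 2 reads "We will provide both the continuous and categorized value for data analysis". It is attached to B1 to B5 and to E1. A1 carries only footnote 3.

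Section 2.3.4 keeps the same outcomes for follow-up and states "Analysis will center on changes in the core indicators over time" and "we will not attempt to test whether changes are statistically significant". The third aim in Section 2.1 depends on this follow-up: "To assess the feasibility and effectiveness (in the short-medium term) of context-led health systems innovations to improve diabetes care locally".

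**The concern.** A1 serves two purposes. As a measure of guideline implementation at baseline, the proportion at target is the natural summary. As a measure of change over a two-year follow-up, it has two weaknesses.

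- **Improvement short of the target is lost.** A patient who goes from 11% to 8.5% counts the same as one who does not change.
- **The target itself can move.** Duration of disease only increases, and complications accumulate. Someone with HbA1c 7.5% in both periods who passes 15 years since diagnosis, or meets the complications and comorbidity condition, goes from not controlled to controlled with no change in glycemia. In the second case a worsening of disease would be read as an improvement in A1.

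Since no significance test is planned, the observed size of change is the whole quantitative evidence for the third aim. It also prompts the second set of focus groups, which discuss whether innovations succeeded.

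**Working it through.** **1. The plan's own figure.** Inputs from Section 2.3.1: proportion 50%, precision ±5 points, design effect 1.2, loss 20%; 95% confidence.
- n = 1.96² × 0.5 × 0.5 / 0.05² = 384.
- × 1.2 = 461; / 0.8 = 576 per setting; × 2 = 1152.

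This reproduces the stated sample size, which is not in dispute.

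**2. Is the yes/no form a stated choice?** Table 2 says which indicators are analysed in both continuous and categorized form, and A1 is not among them. The only regression named in Section 2.3.1 is logistic. No mean, median or change in HbA1c is planned anywhere in the article. So the form is stated, not merely left open.

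**3. Illustrations.** The article gives no HbA1c mean, SD or within-patient correlation. What follows assumes HbA1c ~ Normal(8.5, 2) unless noted.

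*Fall confined to poorly controlled patients.* P(X > 9) = 1 − Φ(0.25) = 40.1%. If each of them falls by exactly 1 point, the mean falls by 0.401 × 1 = 0.40. None of them goes below 8%, so the share below 7% stays at Φ(−0.75) = 22.7% and the share below 8% stays at Φ(−0.25) = 40.1%.

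*Uniform fall of the same mean size.* The share below 7% becomes Φ((7 − 8.1)/2) = Φ(−0.55) = 29.1%, a rise of 6.5 points. A1 does register this.

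*Range for a uniform fall d.* With p0 = Φ((7 − m)/s) and p1 = Φ((7 − m + d)/s), the share of uncontrolled patients who stay above 7% is 1 − (p1 − p0)/(1 − p0). For m = 8, s = 2, d = 0.5: 1 − (0.401 − 0.309)/0.691 = 87%. Over means 7.5 to 9.0 and SDs 1.5 to 2.0:

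| Uniform fall | Stay above 7% | Rise in share below 7% |
|---|---|---|
| 0.3 | 88–96% | 3.7–7.8 points |
| 0.5 | 79–93% | 6.7–13.1 points |
| 1.0 | 59–82% | 15.0–26.1 points |

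*Moving target.* P(7 ≤ X < 8) = 40.1% − 22.7% = 17.5% (unrounded 0.4013 − 0.2266). If the relaxed target is reapplied in each period and, say, 10% of the cohort newly qualifies, A1 rises by 0.10 × 17.5 = 1.7 points with every HbA1c unchanged. The 10% is an assumption; the effect is proportional to it.

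**4. Information kept by the cut.** For a uniform shift, the efficiency of a cut c relative to the mean is f(c)² × SD² / [p(1 − p)].
- Normal shape: 64%, 58% and 49% when 50%, 30% and 20% are controlled. For paired change with correlation 0.6 and the range of means and SDs in the table, the binary form keeps about 22–43%.
- Right-skewed shapes with the same mean 8.5 and SD 2 (gamma with minimum 4.5 or 5, lognormal with minimum 4), cut at 7% or 8%: about 75% to 128%.

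The loss is therefore large under one plausible shape and small or absent under another.

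**5. Precision of the proposed mean change.** Half-width = 1.96 × 2 × √(2(1 − r)) × √(1.2/n). For r from 0.7 to 0.5 this is ±0.15 to ±0.20 with n = 461, and ±0.19 to ±0.25 with n = 300.

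**The case against.** The case on the other side has several parts.

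- **Detail left to an analysis plan.** Section 2.3.1 promises descriptive statistics by variable type, which could cover a mean HbA1c, and refers to the registry for more on outcomes. The raw values are kept, so nothing is lost for good. This lowers the severity. It does not remove the point, because Table 2 chooses which indicators get both forms and leaves A1 out.
- **The proportion fits the guideline aim.** This stands. A1 should be kept, and nothing here suggests that it is wrong for that purpose.
- **A1 combines different tests.** The yes/no status lets patients with HbA1c, fasting glucose or postprandial glucose be pooled; a change in HbA1c cannot. This also stands. HbA1c testing is itself a primary outcome (B6) that innovations may alter, so patients with HbA1c in both periods may be selected by the care they received. That is a real limit of the remedy.
- **A1 is not the only clinical signal.** It is one of 17 primary indicators, beside a continuous quality-of-life score, and E2 counts hospital admissions for glycemic decompensation.

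A reader might infer that real falls in HbA1c are invisible to the study. That goes too far: it holds for individuals who do not cross the target, while a fall across the whole cohort moves A1. A reader might also infer that a fixed share of the sample is in effect discarded. That rests on a normal HbA1c, which the article does not establish; right-skewed shapes give a quite different answer. Nor does the article support a claim that most benefit would occur above the target, since it gives no baseline distribution and the innovations are not yet defined.

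**Conclusion.** The concern holds in a limited form. A1 is fixed as a proportion, follow-up centers on its change, and the HbA1c values that would show change below the level of target crossing are already collected. Two consequences follow from the definition alone: improvement in patients who stay above the target is not recorded in A1, and, if the relaxed target is applied anew in each period, status can improve with no fall in HbA1c.

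Their size cannot be fixed from the article. Under the assumed normal distributions, 79–93% of uncontrolled patients would keep their status after a uniform 0.5-point fall, yet the proportion controlled would still rise by 6.7 to 13.1 points. No single figure for lost information is defensible without the HbA1c distribution. The point matters for the third aim and hardly for the first. It is a worthwhile improvement at little cost, not a flaw that invalidates A1 or the sample size.

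**What to change.** Keep A1 as the guideline indicator. For the follow-up aim, add:

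1. The last HbA1c of each period as a continuous value: mean with SD, or median with IQR if skewed, by district and socioeconomic group.
2. The mean within-patient change in HbA1c with a 95% CI that allows for the sampling design. This is estimation and does not conflict with the decision in Section 2.3.4 not to test.
3. The number of patients with HbA1c in both periods, and a comparison of their characteristics with those of the other patients, because this subset may be selected through access to testing (B6).
4. Optionally, a linear model of the continuous value beside the logistic model for A1.

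The cost is analysis wording and a few table rows; no new data or larger sample is needed. The downside is that the change covers only patients with HbA1c in both periods. Showing their number and characteristics makes possible selection visible but does not remove it, so A1 and the continuous change should be read together.
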